#### Eligibility criteria for inclusion of participants

Participants aged 15 years or older, diagnosed with drug-sensitive pulmonary TB (smear positive or negative) in the last 4 weeks, currently smoking tobacco daily or have only stopped or reduced smoking (less than daily) since diagnosed with TB, willing to quit tobacco use, have access to personal mobile phone and willing and able to provide written informed consent (online supplemental file 1) will be included in the study. A smoker in this trial will be defined as ‘a TB patient who smokes cigarette, and/or biddi, and/or water pipe sessions daily, which means at least 25 days in last month; this does not include heated tobacco products for example, e-cigarettes’. A smoker, as per the mentioned definition, also using smokeless tobacco will be eligible to participate in the trial. Informed consent will be taken from adult participants (18 years and above), while assent along with parent/guardian’s consent will be taken for adolescent participants (15–17 years of age). Exclusion criteria include patients anticipated to have adverse effects either due to the study treatment or research burden. These will include those who are/have less than 15 years of age, retreatment TB, multidrug-resistant TB, miliary or extrapulmonary TB, currently using any pharmacotherapy for tobacco dependence and unwilling or unable to provide written informed consent.

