#### Secondary outcomes

The secondary outcomes include: point abstinence, defined as a self-report of not using tobacco in the previous 7 days, assessed at week 9 and month 6; Adherence to TB treatment: All registered patients with TB’s medication logs (for anti-TB medication) are recorded on the ‘Treatment Support Card’; a copy of this card would be requested from the TB paramedic by the RA and attached with the patient CRF; TB Programme outcomes: the proportion of treatment success (including cured and completed treatment), treatment failure, defaulted and died will be recorded from the TB register (TB03) at month 6; and Economic evaluation. Table 1 gives definitions of TB treatment outcomes.

**Table 1 T1:** Definitions of TB treatment outcomes as per guidelines

Sr. no.	TB treatment outcomes	Definition
1	Cured	A patient who was initially smear-positive and who was smear-negative in the last month of treatment (at month 6) and on at least one previous occasion.
2	Completed treatment	A patient who completed treatment (at month 6) but did not meet the criteria for cure or failure.
3	Treatment failure	A patient who was initially smear-positive and who remained smear-positive at month 6 or later during treatment.
4	Defaulted	A patient whose treatment was interrupted for two consecutive months or more.
5	Died	A patient who died from any cause during treatment.
6	Relapse	A patient who was previously treated for TB, was declared cured or treatment completed at the end of his most recent course of treatment and is now diagnosed with a recurrent episode of TB (either a true relapse or a new episode of TB caused by reinfection).

TB, tuberculosis.

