### Study assessments

All study participants will have assessments on day 0, week 9 and month 6 time points corresponding with routine TB clinic visits. All the trial activities will be performed by field RAs (one RA per site) who will be hired and trained to take patient consent, collect baseline data, follow-up data and perform study assessments. The trial assessment schedule, given as table 2, outlines the visit dates necessary for data collection, but the patient may be seen more frequently for routine clinical care as needed. During the treatment period, if study participants are unable to attend on the day, every effort would be made to complete the visit within 2 days of the scheduled date. If a scheduled visit is missed without notice, then the RA should endeavour to contact the patient by phone or by home visit.

**Table 2 T2:** Participant enrolment and follow-up assessment schedule for Quit4TB trial

Assessment	Screening	Day 0 baseline	Week 9	Month 6
Assessment of eligibility criteria	⌧			
Written informed consent	⌧			
Face-to-face/phone-based interaction			⌧	
Self-reported tobacco use/abstinence status		⌧	⌧	⌧
CO measurement				⌧
Sociodemographic information		⌧		
Tobacco use and quit history		⌧		
Nicotine dependency		⌧	⌧	⌧
Economic outcomes		⌧		⌧
Process outcomes (fidelity)			⌧	⌧
Medication (TB) compliance			⌧	⌧
Adverse events review			⌧	⌧
TB outcomes				⌧

CO, carbon monoxide; TB, tuberculosis.

During the follow-up phase, scheduled assessments will be carried out no more than 5 days before the scheduled visit. Scheduled visits will be rescheduled to allow for public holidays or other unavoidable circumstances that affect the scheduled visit date, but the rescheduled visit should be no more than 5 days from the originally scheduled visit date. Participants will also be given a card with the contact details for the trial RA and the clinical TB care team at their site. If a patient is more than 5 days late for a scheduled study visit, an additional visit will be performed as soon as possible, including the appropriate assessments that were specified in the trial schedule for the visit that was missed.

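### A single TB03 register reading at month 6 cannot finally classify late interrupters, delayed completers or late failures under Table 1's own definitions

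*Protocol article*

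**What the plan says.** Under Secondary outcomes, the protocol article lists treatment success (cured plus completed), and then "treatment failure, defaulted and died will be recorded from the TB register (TB03) at month 6". Table 2 in Study assessments marks TB outcomes in the month 6 column only. The article mentions no later register reading.

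Table 1 supplies the definitions:

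- **Cured:** initially smear-positive, then "smear-negative in the last month of treatment (at month 6) and on at least one previous occasion".
- **Completed:** "A patient who completed treatment (at month 6) but did not meet the criteria for cure or failure".
- **Failure:** initially smear-positive and "remained smear-positive at month 6 or later during treatment".
- **Defaulted:** "A patient whose treatment was interrupted for two consecutive months or more".

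Two other statements fix the clock. Participants may be enrolled if "diagnosed with drug-sensitive pulmonary TB (smear positive or negative) in the last 4 weeks". Study visits run from day 0 through week 9 to month 6, and "scheduled assessments will be carried out no more than 5 days before the scheduled visit"; a rescheduled visit may fall up to 5 days from the planned date. The article does not say whether month 6 in Table 1 counts from the start of treatment or from day 0 of the trial.

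**The concern.** The reading falls at about the time the course is due to end, but three of the Table 1 outcomes can need more time than that. Default takes two months to establish once a patient stops. Completion is delayed by any shorter break. Failure is expressly allowed to come later than month 6. For these patients the month 6 entry is provisional, and Table 1 has no category for a course that is still open.

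Improved health outcomes are part of the trial's stated purpose (Abstract; end of the Introduction), and the message package is meant to improve treatment adherence as well as quitting (section on the mTB-Tobacco intervention). Late interrupters and delayed completers are patients whose adherence the package aims to change. If they are left unclassified, default is undercounted and the success proportion depends on how the unclassified are handled.

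**Working it through.** The plan states no figure on this point to reproduce. The check is timing arithmetic.

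**Inputs**

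- Register reading: trial month 6, taken as six months from day 0 (Secondary outcomes; Table 2).
- Minimum interruption for default: 2 months (Table 1).
- Scheduled end of course: treatment month 6 (Table 1, cured and completed).
- Lag L from diagnosis to day 0: 0 to 4 weeks (Eligibility criteria for inclusion of participants).
- Assumption: treatment starts at diagnosis. The article gives no treatment start date.
- Conversion: 365.25 / 12 / 7 = 4.348 weeks per month, so 4 weeks = 0.92 months.

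**Formulas**

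- Treatment time at the reading: T = 6 + L.
- Latest interruption start that can count as default: T − 2.
- Part of the course in which a new interruption cannot yet count: W = 6 − (T − 2) = 2 − L.
- Share of qualifying interruptions missed, if starts are uniform over six months (assumption): W / 6.

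| Lag L | T (months) | Latest start that counts | W (months) | W / 6 |
|---|---|---|---|---|
| 0 | 6.00 | 4.00 | 2.00 | 33% |
| 2 weeks | 6.46 | 4.46 | 1.54 | 26% |
| 4 weeks | 6.92 | 4.92 | 1.08 | 18% |

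A visit 5 days early or late moves W by about 5 / 30.4 = 0.16 months, or about 3 percentage points. If treatment starts after diagnosis, the slack shrinks. For example, a start one week after day 0 puts the reading at treatment month 5.77 and W at 2.23 months.

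**On-schedule patients.** T is at least 6 for every L from 0 to 4 weeks, so an uninterrupted course has reached its scheduled end by the reading.

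**Delayed completers.** A course extended by breaks that each last under two months is still open at the reading if the total delay exceeds L, that is, 0 to 4 weeks, give or take the 5-day window. Such a patient is not completed, not defaulted, and not a failure unless smear-positive.

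**Effect on the success proportion.** Let N be all participants, S the successes entered by month 6, U the unclassified, and C those among U who later complete. The final proportion is (S + C) / N. Keeping U in the denominator gives S / N at month 6, too low by C / N. Dropping U gives S / (N − U), which need not equal the final value either. The documents give neither U nor C.

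**Reading date that would suffice.** An interruption starting just before treatment month 6 needs a reading at treatment month 8. That is trial month 8 for L = 0, and 8 − 0.92 = 7.08 for L = 4 weeks.

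**The case against.** The strongest reply is that the reading falls at the right time for most patients. Table 1 itself ends the course at month 6, enrolment after diagnosis adds slack, and the visits are planned to coincide with routine TB clinic visits. This stands. A reader might infer that the TB-outcome comparison as a whole rests on unfinished courses, but the article's own figures do not support that.

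A reader might also object that relapse, defined in Table 1 as a previously treated patient who "is now diagnosed with a recurrent episode of TB", cannot occur within this follow-up. That is true but is no defect. Relapse is not among the outcomes the article says will be recorded, Table 1 is presented as a set of guideline definitions, and the relapse rates in the Introduction are background.

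Third, relabelling a late interrupter as defaulted leaves the success proportion unchanged, provided that patient stays in the denominator. This is correct. For that group the error is in the default proportion; only delayed completers move success, and late failures move the failure proportion.

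Fourth, adherence is also recorded from the Treatment Support Card, and TB medication compliance is assessed at week 9 and month 6. These data may show late non-adherence, but they do not supply the missing final outcome.

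Finally, the article condenses a fuller protocol that may hold a later register check. That is possible. But the single month 6 reading is stated in both the text and Table 2, so the mismatch with Table 1 lies in what is written and does not depend on omitted detail.

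**Conclusion.** The point holds for a limited group. With one reading at month 6, interruptions that begin in about the last 1 to 2 months of the course cannot be entered as default, delayed completers have no category, and failures declared later are not captured. Default is undercounted, and success can be understated through the delayed completers.

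The 18% to 33% range is a share of defaults, not of participants. It rests on treatment starting at diagnosis and on uniform start times; one third is the upper end, reached only if everyone enrols at diagnosis. With no rate of default, late interruption or delay in the document, the effect on any reported proportion cannot be computed.

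Because the package targets adherence, a reader might infer a bias between arms. The error could differ by arm, but nothing in the document shows that it does or in which direction. The affected outcome is secondary; the primary outcome and sample size are untouched.

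**What to change.** Keep the abstinence visit at month 6 and separate the TB outcome from it:

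1. Define the TB programme outcome as the final TB03 entry for the course, extracted for every participant in both arms at one fixed later time, trial month 8 or later.
2. State that month 6 in Table 1 counts from the start of treatment, and record the treatment start date so that the two clocks can be reconciled.
3. Report courses still open at extraction as their own category, and keep them in the denominator of every proportion.

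The cost is one later register extraction per centre, with no patient visit, and reporting of this secondary outcome about two months later. It may need cover in the existing approvals. The decision to start phase 4 depends on whether the intervention helps patients quit, so it need not wait for the later extraction.

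### Table 1 cannot class an initially smear-negative patient as a treatment failure, so a completer with a positive month-6 smear counts as a treatment success

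*Protocol article*

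**What the plan says.** Under the participant eligibility criteria, the protocol article admits patients "diagnosed with drug-sensitive pulmonary TB (smear positive or negative) in the last 4 weeks". Both smear groups are therefore in the trial population.

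The Secondary outcomes section names the TB programme outcomes as "the proportion of treatment success (including cured and completed treatment), treatment failure, defaulted and died", and says that these "will be recorded from the TB register (TB03) at month 6". Table 1, titled "Definitions of TB treatment outcomes as per guidelines", then defines the categories:

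- Cure is limited to patients with a positive smear at the start whose smear is negative in the final month and was negative at least once before that.
- Treatment failure: "A patient who was initially smear-positive and who remained smear-positive at month 6 or later during treatment".
- Completed treatment: "A patient who completed treatment (at month 6) but did not meet the criteria for cure or failure".

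No row of Table 1, and no other part of the article, provides for a patient who starts smear-negative and is smear-positive at month 6.

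**The concern.** The eligibility rule and the outcome definitions do not fit together. For one of the two enrolled smear groups, failure is ruled out by definition. The category that absorbs these patients is one of the two that make up treatment success, so a positive smear at the end of treatment would be scored in the favourable direction.

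The trial aims to show improved health outcomes as well as smoking abstinence, and treatment success and failure are among its named TB outcomes. A rule that counts a known positive month-6 smear as success overstates success and understates failure in the patients concerned. An analysis plan that applied Table 1 faithfully would carry the error forward, so this is a matter of what the article states and not of detail left to another document.

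**Working it through.** The article gives no figure to reproduce here. The check is to apply the Table 1 definitions to every smear pattern among patients who are alive, have not defaulted and have completed treatment. There are 2 × 2 × 2 = 8 patterns: initial smear, any earlier negative smear, and month-6 smear. The failure row can be read in two ways:

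- broad: positive at the start and positive at month 6;
- strict: positive at the start and never converted.

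| Initial smear | Earlier negative smear | Month-6 smear | Broad reading | Strict reading |
|---|---|---|---|---|
| + | yes | + | failure | completed (success) |
| + | yes | − | cured | cured |
| + | no | + | failure | failure |
| + | no | − | completed (success) | completed (success) |
| − | yes | + | completed (success) | completed (success) |
| − | yes | − | completed (success) | completed (success) |
| − | no | + | completed (success) | completed (success) |
| − | no | − | completed (success) | completed (success) |

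Two results follow.

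1. All four initially smear-negative patterns end in completed treatment, whatever the month-6 smear and under either reading. Two of the four have a positive month-6 smear.
2. The only pattern on which the readings differ is the initially smear-positive patient who converts and is positive again at month 6: failure on the broad reading, success on the strict one.

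Size. The documents give neither the share of patients who start smear-negative (*s*) nor the proportion of those who complete with a known positive month-6 smear (*c*). The part of the success proportion made up of such patients is *s* × *c*. Assuming *s* between 10% and 50% and *c* between 1% and 5%:

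- lowest: 0.10 × 0.01 = 0.001, or 0.1 percentage points;
- highest: 0.50 × 0.05 = 0.025, or 2.5 percentage points.

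Both ranges are assumptions. Where no month-6 smear is taken in initially smear-negative patients, *c* is zero and so is the effect.

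**The case against.** The strongest reply is that the trial does not classify these patients itself. The category is taken from the TB03 register, and Table 1 reports programme definitions. Programme staff may class such a patient differently in practice, and whether Table 1 departs from its source guideline cannot be judged from the article. This limits what can be said about the data that will be recorded. It does not repair the rule: if the register follows Table 1, the misclassification stands; if it does not, register and protocol disagree and nothing says which prevails.

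A second reply is that the route may be nearly empty. The assessment schedule in Table 2 lists TB outcomes at month 6 but no smear test, and nothing requires a month-6 smear in patients who started negative. That stands. The documents show that such a patient can be counted as a success, not that any will be.

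Four stronger readings are tempting, and the documents do not support them:

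- A reader might infer that every reversion is scored as success. That holds only on the strict reading; on the broad reading these patients are failures.
- A reader might infer that a large share of all positive month-6 smears is miscoded. That needs the smear-negative share and the positivity rate in each smear group, and neither is given.
- A reader might infer that any difference between arms is pulled towards zero. That depends on the scale. Suppose true failure is 5% against 3%, and 40% of failures in each arm are miscoded. The observed figures are 5% × 0.6 = 3% and 3% × 0.6 = 1.8%. The risk ratio is 0.60 before and after. The odds ratio, the scale of the planned logistic model, moves from (0.03/0.97)/(0.05/0.95) = 0.588 to (0.018/0.982)/(0.03/0.97) = 0.593. Only the absolute difference shrinks clearly, from 2.0 to 1.2 points.
- A reader might see a further fault in the relapse row of Table 1. Relapse is not among the proportions to be reported, so the row has no effect on the analysis.

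**Conclusion.** The point holds in a limited form. Under the stated definitions, an initially smear-negative patient who completes treatment and has a positive month-6 smear is a treatment success and cannot be a failure. This follows from the eligibility rule and Table 1 alone and does not depend on how the failure row is read. The class of a patient who converts and reverts is unclear.

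The consequence is confined to a secondary outcome. The primary abstinence outcome, the sample size and the decision to proceed to phase 4 are untouched. The size cannot be computed from the documents; the range of 0.1 to 2.5 percentage points rests wholly on the assumed inputs and on smear results being available. The effect is probably small, but the rule points the wrong way and is cheap to correct.

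**What to change.** Reconcile Table 1 with the eligibility rule, for outcome coding only:

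- State that a patient with a known positive smear at month 6 is not counted in completed treatment or in treatment success, whatever the baseline smear status.
- Say whether remaining smear-positive includes a patient who converted and then reverted.
- State whether Table 1 or the TB03 register category governs when the two differ.
- Apply the coding to smear results already recorded, and carry the same wording into the case report form coding.

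The cost is a change of wording and coding, plus checking the smear results on file against the register category. No new patients, visits or tests are needed. The downside is that the reported success proportion may fall slightly and may differ from the register category in a few patients, which the report should then explain.

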### Study assessments

All study participants will have assessments on day 0, week 9 and month 6 time points corresponding with routine TB clinic visits. All the trial activities will be performed by field RAs (one RA per site) who will be hired and trained to take patient consent, collect baseline data, follow-up data and perform study assessments. The trial assessment schedule, given as table 2, outlines the visit dates necessary for data collection, but the patient may be seen more frequently for routine clinical care as needed. During the treatment period, if study participants are unable to attend on the day, every effort would be made to complete the visit within 2 days of the scheduled date. If a scheduled visit is missed without notice, then the RA should endeavour to contact the patient by phone or by home visit.

**Table 2 T2:** Participant enrolment and follow-up assessment schedule for Quit4TB trial

Assessment	Screening	Day 0 baseline	Week 9	Month 6
Assessment of eligibility criteria	⌧			
Written informed consent	⌧			
Face-to-face/phone-based interaction			⌧	
Self-reported tobacco use/abstinence status		⌧	⌧	⌧
CO measurement				⌧
Sociodemographic information		⌧		
Tobacco use and quit history		⌧		
Nicotine dependency		⌧	⌧	⌧
Economic outcomes		⌧		⌧
Process outcomes (fidelity)			⌧	⌧
Medication (TB) compliance			⌧	⌧
Adverse events review			⌧	⌧
TB outcomes				⌧

CO, carbon monoxide; TB, tuberculosis.

During the follow-up phase, scheduled assessments will be carried out no more than 5 days before the scheduled visit. Scheduled visits will be rescheduled to allow for public holidays or other unavoidable circumstances that affect the scheduled visit date, but the rescheduled visit should be no more than 5 days from the originally scheduled visit date. Participants will also be given a card with the contact details for the trial RA and the clinical TB care team at their site. If a patient is more than 5 days late for a scheduled study visit, an additional visit will be performed as soon as possible, including the appropriate assessments that were specified in the trial schedule for the visit that was missed.

### Weekly monitoring calls

For intervention fidelity, the RAs will be responsible for telephonically calling the recruited patients to make sure that they are receiving and reading the messages or getting the messages read to them, daily. Monitoring calls will be weekly for the first 2 months, where most of the intervention will be delivered in this period, followed by biweekly or monthly calls. This will also build rapport between the patient and the research team, which will help in successful follow-ups and outcome assessments.

